### GROWMORE study protocol

#### Hypotheses

1. Muscle oxidative capacity determined by ^31^P MRS and cardiorespiratory fitness are related to measures of physical activity, physical inactivity, insulin resistance and Vitamin D status in adolescence.

2. Auxological measures (weight, height, OFC and skinfold) provide a reliable measure of adiposity compared to non-invasive body composition assessment using air displacement plethysmography (BODPOD™).

3. Intra-hepatic or intra-myocellular lipid accumulation is related to markers of insulin resistance, raised triacylglycerol and measured body fat in adolescents

4. Body composition and metabolic outcomes in adolescence are related to patterns of infant growth, body composition and nutritional intakes.

#### Power calculation

Determining an appropriate sample size for this study is difficult given there are multiple outcome variables, including some exploratory, being investigated. Using results from phase three of this study, we know that insulin sensitivity is strongly associated with fat mass index. Using the effect size from our data of r^2^ = 0.12, with 80% power at the 5% level of significance we estimated that we would need ~60 patients to be able to detect a significant difference. Previous work looking at mitochondrial oxidative function in the Magnetic Resonance centre required a sample size of only 10 patients to determine a 10% reduction in τ_1/2_ PCr [34]. Therefore we have chosen to study 60 young people, as this will ensure an adequate sample size for two of the main outcome variables.

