We will use custom-built exercise apparatus to allow each participant to perform a standardised exercise protocol as previously described by members of our group [34,53,54], consisting of plantar flexion against fixed resistance during which time 31 P-MRS will be used to assess mitochondrial oxidative function (see Figure 2. In order to generate the ^31^P spectra, a 10 cm diameter ^31^P surface coil will be placed over the calf muscles, centred on the widest part of the gastrocnemius/soleus complex, for transmission and reception of the signal. After calf muscle group maximum voluntary contraction (MVC) has been determined for each participant, the exercise apparatus will be set to provide resistance of 35% of MVC, and ^31^P spectra will be recorded over a three minute time window to assess resting mitochondrial function. This will be immediately followed by a three-minute exercise period during which the participants will be required to perform plantar flexion against the set resistance at a frequency of 0.5 Hz and then a further rest period. MR phosphorous spectra will be collected every 10 seconds during the protocol using adiabatic One-Dimensional Image-Selected In-vivo Spectroscopy (1D-ISIS). This protocol has been shown to robustly measure mitochondrial oxidative function during recovery from exercise [34,53].

The phosphorus spectra will be analysed in batches using the Advanced Method for Accurate, Robust and Efficient Spectral fitting (AMARES) algorithm [56] and from this quantifications of phosphocreatine (PCr), inorganic phosphate (Pi) and pH throughout the protocol will be obtained. The data will then be processed to calculate the various components of oxidative metabolism as described by Kemp and Radda [57]. The primary outcome measure will be the half-time of PCr recovery [53] (τ_1/2_ PCr). This recovery period is used to measure mitochondrial oxidative phosphorylation ‘capacity.’ In addition, the half-time of ADP (τ_1/2_ ADP) recovery will be measured as it provides a similar measure to τ_1/2_ PCr but may be more resistant to heterogenous pH responses at the end of exercise.

7. **Physical activity levels**

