#### Statistical analysis

Data will be analysed using Stata (v11, StatCorp LP, Texas, USA). Mann–Whitney U or t tests will be used to demonstrate that the follow-up sample is broadly representative of the original cohort for key variables such as gestation and birth weight. Correlation analysis will be used to examine the relationships between the different measures of body composition and the MR measures of lipid deposition and to examine the interaction between vitamin D and oxidative capacity by ^31^P MRS and cardiorespiratory fitness. To assess associations between infant and childhood growth and subsequent metabolic outcomes, we will develop separate linear regression analysis models using insulin sensitivity and body composition (fat mass index and lean mass index) as the dependent variables. Half-time of PCr recovery (τ_1/2_ PCr) will be used as dependent variable for regression models examining muscle mitochondrial function in relation to insulin sensitivity, directly measured exercise, body composition and vitamin D levels (as independent variables). In all multiple linear regression models adjustment will be made for potential confounding factors such as sex, gestation, age at follow-up, birthweight z-score, infant growth velocity, post discharge feeding pubertal status and whether mechanical ventilation was required in the neonatal period (which we used as a proxy for illness severity). Bland Altman analysis will be used to assess agreement between the different techniques used to assess body composition.

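### The claim that 60 participants is adequate for PCr half-time rests on a sample size for a mean reduction, whereas the plan only tests associations

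*Protocol article*

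**What the plan says.** The Power calculation section gives two arguments for the sample size. The first concerns insulin sensitivity and fat mass index: "Using the effect size from our data of r^2^ = 0.12, with 80% power at the 5% level of significance", about 60 participants are needed. The second concerns PCr half-time: "Previous work looking at mitochondrial oxidative function in the Magnetic Resonance centre required a sample size of only 10 patients to determine a 10% reduction". It gives no standard deviation, power, significance level, design or comparator. The section then concludes, "Therefore we have chosen to study 60 young people", and gives as its reason: "as this will ensure an adequate sample size for two of the main outcome variables". The two outcomes are not named, but only insulin sensitivity and PCr half-time have been discussed at that point.

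The subsection on measurement of mitochondrial oxidative function states: "The primary outcome measure will be the half-time of PCr recovery".

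The use planned for this outcome appears in three places:
- **Hypotheses, item 1:** muscle oxidative capacity is related to activity, inactivity, insulin resistance and vitamin D status.
- **Study design:** all initial assessments take place in one morning, and no second PCr measurement is described.
- **Statistical analysis:** PCr half-time "will be used as dependent variable for regression models examining muscle mitochondrial function" against insulin sensitivity, exercise, body composition and vitamin D. Eight confounders are named, as examples. A correlation between vitamin D and oxidative capacity is planned as well.

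**The concern.** The number 10 answers a different question from the one this study asks. Detecting a 10% mean reduction depends on the size of the shift relative to the standard deviation of a change or of a group difference. Detecting an association depends on how much of the between-person variation in PCr half-time is explained by activity, vitamin D or insulin sensitivity. The first quantity does not fix the second.

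The interpretation of null results is at stake. Setting 60 beside 10 suggests a wide margin. If PCr half-time shows no association with activity or vitamin D, a reader who relies on the adequacy statement may take that as evidence of no relationship. The protocol has not said how large an association the study could detect for this outcome.

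**Working it through.** **Inputs from the protocol.** n = 60; r² = 0.12 for insulin sensitivity with fat mass index; 80% power; 5% significance (two-sided assumed, as sidedness is not stated); 10 patients for a 10% reduction in PCr half-time; eight named adjusters and four exposures. No expected association is given for PCr half-time, so the values of r in step 4 are assumptions.

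**1. The protocol's own figure.** With f² = r²/(1 − r²) = 0.12/0.88 = 0.136 and a noncentral F test of one predictor (λ = n·f²), n = 60 gives power 0.803, so the figure of about 60 reproduces. Fisher z gives n = [(1.960 + 0.842)/atanh(0.346)]² + 3 = (2.802/0.361)² + 3 = 63.1, which rounds up to 64; its power at 60 is 0.78. The insulin sensitivity argument stands.

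**2. What 10 patients for a 10% reduction would imply.** This assumes 80% power and two-sided 5%, neither of which the protocol states for this figure.

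| Reading of 10 | Standardised effect needed | Implied variability |
|---|---|---|
| 10 paired differences | 0.996 | SD of differences 10/0.996 = 10.0% |
| 10 per group | 1.325 | between-person CV 10/1.325 = 7.5% |
| 5 per group | 2.02 | between-person CV 10/2.02 = 4.9% |

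The protocol does not say which reading applies. None of them yields a correlation or a slope.

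**3. Ten patients under the planned type of test.** The smallest correlation detectable at n = 10 (Fisher z) is tanh(2.802/√7) = tanh(1.059) = 0.79. Ten would be enough only for a very strong association, so the comparison of 60 with 10 does not measure any margin here.

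**4. Sixty participants under the planned tests.** Smallest detectable association at 80% power and two-sided 5%:

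| Method | Unadjusted r² | Partial r², 8-12 adjusters |
|---|---|---|
| Noncentral F, λ = n·f² | 0.119 | 0.12 |
| Noncentral F, λ = residual df·f² | 0.123 | 0.14-0.15 |
| Fisher z, tanh²(2.802/√(57 − adjusters)) | 0.126 | 0.145-0.156 |

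For the Fisher row, the unadjusted value is tanh²(2.802/√57) = tanh²(0.371) = 0.126. With 12 adjusters it is tanh²(2.802/√45) = tanh²(0.418) = 0.156.

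Unadjusted power at 60 is Φ(atanh(r)·√57 − 1.960):

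| Assumed r | atanh(r)·√57 | Power at 60 | n for 80% power |
|---|---|---|---|
| 0.2 | 1.531 | 33% | 194 |
| 0.3 | 2.337 | 65% | 85 |
| 0.4 | 3.198 | 89% | 47 |

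**The case against.** The strongest reply is that the 10-patient sentence does not drive the design. The target of 60 comes from the insulin sensitivity calculation, which reproduces, and removing the sentence would change neither enrolment nor any analysis. The section also admits that sample size is difficult to set with several outcomes, some of them exploratory. All of this is correct, and it limits the point to one statement in the text.

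Two qualifications also stand. The word primary appears inside the spectroscopy subsection, next to the ADP half-time, and may mean primary among the spectroscopy measures. That the second adequately sized outcome is PCr half-time is an inference from the surrounding sentences, though no other reading is evident.

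It could be argued that the regression contains group terms such as sex and post-discharge feeding. These enter as confounders; the document plans no contrast of PCr half-time between such groups as the test of interest.

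A reader might infer three stronger claims that the documents do not support:
- **That 60 is too small.** The protocol states no expected association for PCr half-time. If the true partial r is about 0.35-0.39 or more, 60 is enough.
- **That 10 patients is credible only for within-person change.** The earlier study's design is not given, and 10 per group with a between-person CV of about 7.5% would fit equally well.
- **That power for a 10% difference between two halves of the sample is poor.** No such split is planned and the protocol gives no CV. The answer depends wholly on the value assumed: power is about 48% at a CV of 20% and about 97% at 10%.

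**Conclusion.** The point holds as a mismatch between the effect size cited and the analysis planned. It is not an arithmetic error, since no stated number is miscalculated. The adequacy claim for PCr half-time has no basis for the tests that will be run. The supportable statement is that 60 participants give 80% power for r² of about 0.12-0.13 unadjusted, or partial r² of about 0.12-0.16 after adjustment, and that assumed correlations of 0.2-0.3 would be detected with only 33-65% power.

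These figures assume a two-sided 5% test, all 60 participants with usable spectra, and 8-12 adjusters. The adjuster count is not fixed, because the protocol's list is given as examples. The adjusted figure depends on the method: with λ = n·f², adjustment hardly changes it.

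**What to change.** Delete the sentence on 10 patients and a 10% reduction. Then do one of the following:

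1. Limit the adequacy statement to insulin sensitivity.
2. State the smallest association of PCr half-time detectable at n = 60 with 80% power at two-sided 5%, and name the method. Suitable figures are r² of about 0.12-0.13 for the unadjusted vitamin D correlation and, for the adjusted regressions, the partial r² from the chosen method: 0.12 (noncentral F, λ = n·f²), 0.14-0.15 (λ based on residual degrees of freedom) or 0.14-0.16 (Fisher z). Giving the same figure at the expected number of usable spectra would also help.

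The cost is about two sentences and a less favourable statement of power. Enrolment, assessments and planned analyses do not change.

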#### Current study population and recruitment

All children who participated in phase 3 (n = 153) will be approached, via mail, after verifying postal address through their general practitioner. We will approach the young people sequentially starting with the oldest, but no other active selection process will be used. A recruitment letter, explaining the study and assessments in detail will be sent to all parents whose children fit the above criteria and a simplified patient information sheet sent to the young person. Informed, written consent will be obtained from parents and where appropriate, participants, before participation.

#### Study design

The same researcher (RT) will carry out all assessments. Figure 1 shows the study protocol flowchart. All initial assessments will be carried out during a single morning visit to the Newcastle Magnetic Resonance Imaging Centre. Participants will attend fasted. Once the initial assessment is finished (within 4 hours), the pre-programmed accelerometers (Actigraphs) will be given to each young person to wear for 3 days and a feedback questionnaire given. The Actigraph and questionnaires will then be returned and data analysed.

**Figure 1 F1:**
[figure not shown]
The study protocol flowchart.

We will use the following methods during assessment:

1. **Anthropometry**

• Height will be measured to the nearest 0.1 cm, using a telescopic stadiometer (SECA, Birmingham, UK)

• Weight will be taken to the nearest 0.1 kg from the BODPOD**™ (**Cosmed, USA). BMI will be calculated using these measurements. Standard deviation scores will be calculated for height, weight and BMI using standard reference data.

• Waist circumference will be measured using a measuring tape (CTO Group, China).

• Weight and height standard deviation scores, adjusted for sex and age will be calculated using the LMS calculator and British 1990 growth reference standards [35,36].

• Blood pressure will be taken from the right arm, using an automated sphygmomanometer. (Carescape vital signs monitor, GE Healthcare systems, UK)

2. **Body composition**

Initially, Holtain calipers (Crymych, UK) will be used to measure skinfold thickness in four areas- biceps, triceps, subscapular and suprailiac. These will be used to generate an estimate of body density [37,38]. A second estimate of body composition will also be made using BODPOD™ [39,40]. The BODPOD uses air displacement plethysmography and has been validated for use in children [41]. BODPOD measures body mass and volume by calculating differences in volume of the participants compared to calibration volumes (age-dependent) of the participant sitting inside the BODPOD, thus allowing body density to be calculated. Once overall body density is determined, the relative proportions of lean and fat body mass can be calculated.

3. **Biochemistry and insulin sensitivity**

All participants will attend fasted. Baseline bloods will be taken (for lipid profile, liver function, glucose, insulin, sex hormones, RNA, cellular DNA and serum to store) and then a standardised fasting-state oral glucose tolerance test will be performed [42]. Insulin sensitivity and resistance will be measured using the Homeostasis Model Assessment (HOMA) method.

Sinha et al. [34] have also demonstrated a clear association between skeletal muscle mitochondrial oxidative function and serum vitamin D levels in patients with Growth Hormone deficiency using the same 31-P MRS exercise protocol as we will use. In order to ensure we can control our data for any influence of vitamin D status, frozen serum will be assayed using a Liquid Chromatography-Tandem Mass Spectrometry (LC-MS/MS) method to obtain a 25-OH Vitamin D quantification.

4. **Epigenetic sampling**

We will seek consent to store any spare serum and DNA (extracted from blood and saliva) for future analysis [43,44]. These samples will be subject to the Human Tissue Act 2004 [45] and held under license (issue number 12534, held by Newcastle Biomedicine Biobank). DNA will be extracted at the Institute of Genetic Medicine, Newcastle University, Newcastle-upon –Tyne using standard techniques [46-48].

5. **Measurement of intra-hepatic lipid**

Intra-hepatic lipid (IHL) and Intra-myocellular lipid (IMCL) deposition will be determined using ^1^H magnetic resonance spectroscopy. Details of the planned MR sequences will be similar to those used in our previous work [49]. Percentage of intrahepatic lipid will be calculated using the % of CH_2_ lipid peak signal amplitude, relative to the water peak signal amplitude [50-52].

6. **Measurement of mitochondrial oxidative function**

We will use custom-built exercise apparatus to allow each participant to perform a standardised exercise protocol as previously described by members of our group [34,53,54], consisting of plantar flexion against fixed resistance during which time 31 P-MRS will be used to assess mitochondrial oxidative function (see Figure 2. In order to generate the ^31^P spectra, a 10 cm diameter ^31^P surface coil will be placed over the calf muscles, centred on the widest part of the gastrocnemius/soleus complex, for transmission and reception of the signal. After calf muscle group maximum voluntary contraction (MVC) has been determined for each participant, the exercise apparatus will be set to provide resistance of 35% of MVC, and ^31^P spectra will be recorded over a three minute time window to assess resting mitochondrial function. This will be immediately followed by a three-minute exercise period during which the participants will be required to perform plantar flexion against the set resistance at a frequency of 0.5 Hz and then a further rest period. MR phosphorous spectra will be collected every 10 seconds during the protocol using adiabatic One-Dimensional Image-Selected In-vivo Spectroscopy (1D-ISIS). This protocol has been shown to robustly measure mitochondrial oxidative function during recovery from exercise [34,53].

The phosphorus spectra will be analysed in batches using the Advanced Method for Accurate, Robust and Efficient Spectral fitting (AMARES) algorithm [56] and from this quantifications of phosphocreatine (PCr), inorganic phosphate (Pi) and pH throughout the protocol will be obtained. The data will then be processed to calculate the various components of oxidative metabolism as described by Kemp and Radda [57]. The primary outcome measure will be the half-time of PCr recovery [53] (τ_1/2_ PCr). This recovery period is used to measure mitochondrial oxidative phosphorylation ‘capacity.’ In addition, the half-time of ADP (τ_1/2_ ADP) recovery will be measured as it provides a similar measure to τ_1/2_ PCr but may be more resistant to heterogenous pH responses at the end of exercise.

7. **Physical activity levels**

Physical activity levels over a 24-hour period will be measured using an Actigraph **™**accelerometer (Actigraph, Pensacola, FL). The Actigraph is a small and lightweight monitor that will be worn on the right hip during waking hours for three days. The Actigraph has high validity, reliability, and low reactivity in children [58] and has been used successfully in several paediatric physical activity studies [59]. The accelerometers will be set to record data in 10-second epochs. Analysis of the activity data will be performed using Actilife program (v5, MTI, Pensacola, USA). A written diary will also be kept to monitor periods of non-wear. From the data gained we will calculate the time spent in sedentary or moderate to vigorous physical activity (MVPA). MVPA has been chosen rather than looking individually at different activity levels: it has been shown in a term born group of children in north east England that MVPA seems to be most closely associated with body habitus change when followed longitudinally [60].

8. **Diet and nutritional assessment**

The SCRAN-24 dietary recall program will be used to determine each participant’s food/drink intake over the previous 24 hours. (Human Nutrition Research Centre, Newcastle University) [61]. SCRAN-24 uses a series of steps to determine the times of food/drink intake over the 24 hours prior to using the program. It asks the user to list chronologically the items of food or drink consumed in the 24-hour period under a series of headings (breakfast, mid-morning snack, lunch etc.). It then breaks down each intake into their component parts. For the majority of foodstuffs (98% of those regularly consumed by children in the north east of England), the programme contains a listed item. Non-listed items have to be entered in free-text. Once the items are selected for the full 24-hour period the program then revisits each episode of food intake and prompts the participant to assess and log portion size based on a series of photo-based choices. Pre-programmed nutritional information for each listed item, by portion size is allocated to each item. A final step prompts the user to try to link food and drink intake with activity through the day and highlights any times of the day during which nothing was ingested as particular areas to focus on. This is done to try to improve recall and thus improve the sensitivity of the diary. SCRAN-24 has been validated for use in people in the north east of England aged 11 years of age or over.

9. **Questionnaires**

Intervention questionnaires will also be given to the participants, asking opinions on different potential structured activities within a programme designed to encourage a healthier lifestyle in children and their families. This data will help to inform potential future interventional studies about which interventions might be most accepted by a similar teenage cohort.

**Figure 2 F2:**
[figure not shown]
**Typical 31-P spectra generated during exercise within the MR scanner and the equipment that will be used for the study **[55]**.**

Following the assessment we will give each young person a feedback questionnaire to fill in to assess their experience of the study assessment day and their perceived acceptability of the assessment methods. By reviewing how many participants accept, decline or are unwilling/unable to complete particular assessments we will gauge their usefulness for future trials.

The study has been approved by the Sunderland Research Ethics Committee and the Research and Development Department of Newcastle Hospitals NHS Trust.

#### Statistical analysis

Data will be analysed using Stata (v11, StatCorp LP, Texas, USA). Mann–Whitney U or t tests will be used to demonstrate that the follow-up sample is broadly representative of the original cohort for key variables such as gestation and birth weight. Correlation analysis will be used to examine the relationships between the different measures of body composition and the MR measures of lipid deposition and to examine the interaction between vitamin D and oxidative capacity by ^31^P MRS and cardiorespiratory fitness. To assess associations between infant and childhood growth and subsequent metabolic outcomes, we will develop separate linear regression analysis models using insulin sensitivity and body composition (fat mass index and lean mass index) as the dependent variables. Half-time of PCr recovery (τ_1/2_ PCr) will be used as dependent variable for regression models examining muscle mitochondrial function in relation to insulin sensitivity, directly measured exercise, body composition and vitamin D levels (as independent variables). In all multiple linear regression models adjustment will be made for potential confounding factors such as sex, gestation, age at follow-up, birthweight z-score, infant growth velocity, post discharge feeding pubertal status and whether mechanical ventilation was required in the neonatal period (which we used as a proxy for illness severity). Bland Altman analysis will be used to assess agreement between the different techniques used to assess body composition.

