**Methods/Design:**

This current study, GROWMORE, is the fourth phase of the Newcastle Preterm Birth Growth Study (PTBGS), which was formed from two randomised controlled trials of nutrition in early life in preterm (24–34 weeks gestation) and low birthweight infants. 247 infants were recruited prior to hospital discharge. Infant follow-up included detailed measures of growth, nutritional intake, morbidities and body composition (Dual X Ray Absorptiometry, DXA) along with demographic data until 2 years corrected age. Developmental assessment was performed at 18 months corrected age, and cognitive assessment at 9–10 years of age. Growth, body composition (DXA), blood pressure and metabolic function (insulin resistance and lipid profile) were assessed at 9–13 years of age, and samples obtained for epigenetic analysis. In GROWMORE, we will follow up a representative cohort using established techniques and novel metabolic biomarkers and correlate these with current lifestyle factors including physical activity and dietary intake. We will assess auxology, body composition (BODPOD™), insulin resistance, daily activity levels using Actigraph™ software and use ^31^P and ^1^H magnetic resonance spectroscopy to assess mitochondrial function and intra-hepatic lipid content.

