In the second RCT, the ‘protein study’ , 77 infants were randomised to one of three preterm formulas that were iso-caloric (80 kcal/100 mL), but differed in protein density (A - 3.3 g, B - 3.0 g, and C - 2.7 g per 100 kcal) [31]. Infants were recruited once full enteral feeding had been successfully established and they continued on the trial formula post-discharge until 12 weeks post-term. Milk intake, auxology and serum biochemistries were determined weekly during inpatient stay, and every 4 weeks until 12 weeks. Auxology was repeated 6 monthly until 24 months. Body composition was assessed using DXA at discharge and at 12 weeks.

In both studies, a social questionnaire addressing aspects of family structure, parental employment, education history, smoking etc., was completed prior to hospital discharge. Although the inclusion criteria for randomisation into the two RCTs was a gestational age of ≤34 weeks, 1 set of low birthweight triplets of 36 weeks gestation were included as breastfeeding controls, along with siblings of eligible infants whose birthweight was >1750 g. Because of a small time overlap in the recruitment period for the two RCTs (randomised infants could only join one RCT) there were 4 breast fed control infants who were initially included in study reports for both studies, but thereafter are only included once in the combined cohort. Mean gestation for the cohort (n = 247) was 30.9 weeks (range 24.7-36.4 weeks) and birthweight 1392 g (range 690-2200 g). One hundred and twenty five were male. There were no significant differences in gestation or weight between boys and girls.

The Newcastle PTBGS has previously been followed up on three occasions since the initial randomised controlled trials (see Table 1). The current study, GROWMORE, will be phase four of follow-up [33].

**Table 1 T1:** Data collected during follow-up phases of the Newcastle preterm birth growth study

**Phase 1- Growth and Protein study RCTs**	**Phase 2- Cognitive/Behavioural follow-up at 10 years**	**Phase 3- Early adolescent follow-up**	**Phase 4- Late adolescent follow-up**
**(n = 247)**	**(n = 92 from 113 in growth study)**	**(n = 153 from 247 in RCTs)**	**(n = 60 from 153 in phase 3)**
**Auxology:**		**Auxology:**	**Auxology:**

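### Difference tests cannot demonstrate that the 60 young people studied are representative of the original cohort; report standardised differences with confidence intervals instead

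*Protocol article*

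**What the plan says.** The Statistical analysis section states that Mann–Whitney U or t "tests will be used to demonstrate that the follow-up sample is broadly representative of the original cohort for key variables", and illustrates these as "key variables such as gestation and birth weight". It names no margin, effect size, confidence interval or acceptance criterion for the comparison. It also does not say whether the young people studied are removed from the cohort before being compared with it.

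The abstract, under Methods/Design, already takes the answer as given: "we will follow up a representative cohort using established techniques and novel metabolic biomarkers".

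The sizes are in Study setting and Table 1. The original cohort numbered 247 ("Mean gestation for the cohort (n = 247) was 30.9 weeks"), and the phase 4 column is headed "n = 60 from 153 in phase 3". On how the 60 are reached, Current study population and recruitment says: "We will approach the young people sequentially starting with the oldest, but no other active selection process will be used".

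**The concern.** The purpose given to the tests is to establish similarity, but t and Mann–Whitney tests take similarity as the null hypothesis. The most they can do for the claim is fail to reject it, and with 60 people studied that can easily happen when a real difference exists. The method in the text does not support the conclusion in the text, whatever the data show.

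About a quarter of the original cohort (60/247 = 24%) will be studied, after two stages of selection: attendance at phase 3, then participation in phase 4 with the oldest approached first. The Background gives the study a partly descriptive purpose, namely to learn how these metabolic markers are distributed in high-risk groups. For that purpose it matters directly whom the 60 resemble. A statement that the sample was shown to be representative would carry weight with readers that the test cannot give it.

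**Working it through.** **Inputs.** Original cohort 247 (Study setting); studied 60, drawn from 153 at phase 3 (Table 1). Not studied: 247 − 60 = 187. Phase 3 attenders not studied: 153 − 60 = 93. A two-sided 5% level is assumed. The article gives neither an SD nor an expected shift for these comparisons, so the true difference *d* between studied and not studied is taken as 0.2 to 0.5 SD, with equal SDs and a normal approximation.

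**The plan's own figure.** The article gives no power or margin for the representativeness tests. Its sample size is for another question, the association of insulin sensitivity with fat mass index: "r^2^ = 0.12, with 80% power at the 5% level of significance", from which "we would need ~60 patients to be able to detect a significant difference". That figure reproduces. An F test with one predictor and f² = 0.12/0.88 needs n = 60 (power 80.3%). The Fisher z approximation gives 64. So 60 is sound for its own purpose, but it was not chosen for this comparison.

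**Reading A: studied against not studied (60 v 187, disjoint).**
- SE = √(1/60 + 1/187) = 0.148 SD.
- 95% CI half-width = 1.96 × 0.148 = 0.29 SD.
- Power ≈ 1 − Φ(1.96 − d/SE). At d = 0.3: 0.3/0.1484 = 2.02, giving 52%.
- Power reaches 50% at 1.96 × 0.1484 = 0.29 SD and 80% at (1.96 + 0.84) × 0.1484 = 0.42 SD.

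**Reading B: studied against the whole cohort (60 v 247, the 60 counted twice).**
- The cohort mean is (60 × studied mean + 187 × not-studied mean)/247, so the observed difference is only 187/247 = 0.757 of *d*.
- SE used by the two-sample test = √(1/60 + 1/247) = 0.144. Actual SD of the difference = 0.757 × 0.148 = 0.112.
- The test rejects when the difference exceeds 1.96 × 0.144 = 0.282. With no true difference, 0.282/0.112 = 2.51, so the type I error is about 1.2% instead of 5%.
- At d = 0.3 the expected difference is 0.227, and (0.282 − 0.227)/0.112 = 0.49, giving power of 31%.
- Power reaches 50% at 0.282/0.757 = 0.37 SD and 80% at (0.282 + 0.84 × 0.112)/0.757 = 0.50 SD.

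| True difference (SD) | Power, A: 60 v 187 | Power, B: 60 v 247 with overlap |
|---|---|---|
| 0.2 | 27% | 12% |
| 0.3 | 52% | 31% |
| 0.4 | 77% | 57% |
| 0.5 | 92% | 80% |

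Simulation with 20,000 data sets per scenario agrees. At 0.2, 0.3 and 0.5 SD it gives 27%, 53% and 92% for A, and 12%, 30% and 80% for B. The type I errors are 5.0% and 1.2%.

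**Could similarity be shown formally?** Two one-sided 5% tests on 60 v 187, with no true difference, have 0% power for a margin of 0.2 SD (1.645 × 0.148 = 0.244 already exceeds it), 29% for 0.3 SD and 92% for 0.5 SD. Only a wide margin is within reach.

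**The case against.** The strongest reply is that the claim is modest and little depends on it. The text says *broadly* representative, and a test that finds a 0.5 SD shift 80% to 92% of the time is a reasonable screen for gross selection. The four hypotheses concern associations and agreement between methods within the sample, not cohort means. No planned model depends on passing the test, and the regressions adjust for gestation, birthweight z-score, age at follow-up and post-discharge feeding, among others. An article may also leave the margin and the variable list to a fuller document.

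Most of this stands as a limit on the consequence. It does not rescue the method: a difference test fails to demonstrate similarity however loosely similarity is meant, and the article itself assigns the test that purpose.

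Four stronger readings are tempting, and the document does not support them:
- *That the 60 are certainly compared with a group that includes them.* Reference to the original cohort makes this a natural reading, but a condensed article may mean followed-up against not followed-up. The 1.2% error rate and the lower power figures hold only under reading B.
- *That the tests will usually miss real selection.* This is true only below about 0.29 SD (A) or 0.37 SD (B). The size of any real selection is unknown.
- *That only gestation and birth weight will be examined.* They are given as examples.
- *That adiposity, insulin sensitivity and deprivation are on record for everyone invited.* Table 1 gives phase 3 body composition for 139 and bloods for 109 of 153. It lists the deprivation score under phase 2 (92 of 113, growth study only).

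**Conclusion.** The point holds as one about method and wording. The planned tests cannot demonstrate representativeness, because non-significance is not evidence of similarity and no criterion is stated against which similarity could be judged. This conclusion needs no arithmetic and is the same under either reading of the comparator.

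The size rests on the assumed shifts of 0.2 to 0.5 SD and on 60 people being studied. With disjoint groups, a 0.2 SD shift would be missed about three times in four and a 0.3 SD shift about half the time. A 0.5 SD shift would be missed about one time in twelve. If the groups overlap, the misses rise to 88%, 69% and 20%.

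A reader might infer that the cohort is in fact unrepresentative or that the regression results will be biased. The document supports neither. It shows only that the planned check could not settle the question.

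**What to change.** Drop *demonstrate* from the Statistical analysis section and stop describing the sample as representative in advance in the abstract. In place of the tests, report:

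- **Studied v not studied (about 60 v 187, disjoint):** standardised differences with 95% CIs for gestation and birth weight, for RCT and feeding group (as proportions), and for items from the social questionnaire, which was completed before discharge in both trials. RCT and feeding group belong here because the two trials overlapped only briefly in recruitment. If enrolment stops near 60, an oldest-first approach could favour one trial. Both trials aimed at the same gestation and birthweight limits, so those two variables might not reveal this.
- **Studied v phase 3 attenders not studied (about 60 v 93):** phase 3 body composition and OGTT measures where available, with the numbers shown. If missing data fall in proportion, the 139 with body composition split about 55 v 84, with a half-width of 1.96 × √(1/55 + 1/84) = 0.34 SD. The 109 with bloods split about 43 v 66, with a half-width of 1.96 × √(1/43 + 1/66) = 0.38 SD.

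Then limit the claim to what the intervals exclude. For example, an observed difference of zero in the first comparison would rule out shifts beyond about 0.29 SD and no less. Weighting for participation is an optional sensitivity analysis and would be imprecise with about 60 people.

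The cost is a wording change, one extra table from data collected in earlier phases, and a more cautious claim.
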